#### Exploratory measures

- comparison of the duration of treatment effect in the 2-week placebo crossover period (Week 7 through Week 8) among the treatment arms in subjects who were treatment successes
- comparison between the difference in number of doses of rescue medication used during the Week 0 baseline period and number used during each week of the active treatment period between 2, 4, 8, and 16 mg prosaptide and placebo
- comparison between McGill pain questionnaire differences from the Visit 4 baseline measurement and Week 7 measurements between 2, 4, 8, and 16 mg prosaptide and placebo
- comparison between global physician impression differences from the Visit 4 baseline measurement and Week 7 measurements between 2, 4, 8, and 16 mg prosaptide and placebo

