## 3.1. Overall study design

This will be a randomized, double-blind, placebo-controlled multicenter study design using four dosing levels (2, 4, 8, and 16 mg/day) to evaluate the efficacy and safety of prosaptide for the relief of neuropathic pain associated with HIV-1. An interim analysis will be performed when 200 subjects complete 6 weeks of treatment.

Subjects will be washed out of **adjuvant pain medications** including anticonvulsants, antidepressants, topical analgesics and short-acting narcotics. Long acting opioid analgesics (maintained at a constant daily dose throughout the study) will be permitted in up to 20% of screened subjects at each study site. Subjects taking long-acting narcotics must have received a constant daily dose for at least 30 days prior to Visit 1. All subjects will receive a supply of **acetaminophen 500 mg caplets** as **rescue medication**. Subjects who have intolerable pain despite rescue medication are permitted to discontinue from the study at any time.

The double-blind phase will include a 6 week active treatment phase with subjects receiving one of the 4 dosing levels of prosaptide or placebo as illustrated in Figure 3-1.

Subjects who meet entry criteria, including a pain level of Gracely 0.74 log units averaged over the 2-week period between Visit 2 and Visit 3, and have completed written informed consent will be randomized into the study. Subjects randomized after the **two part** screening phase will complete a one week baseline period, then will receive one of four active treatment or placebo for a **42-day** double-blind treatment period. This will be followed by a **2-week** double-blind **crossover period**, during which subjects previously receiving active treatment will receive placebo injections. **The group receiving placebo during the 42-day double-blind treatment period will be crossed over to receive prosaptide 4 mg for 2 weeks,** forming a modified **cross-over** design*.* The purpose of the crossover period is to assess the duration of prosaptide response after discontinuation of treatment. In addition, it increases the number of subjects who receive active treatment, enhancing the ability to assess the magnitude of the placebo response, and the secondary outcome of early pain response. It also allows all subjects the opportunity to receive active therapy at some point during the study. Study visits will occur every 2 weeks during both double-blind periods.

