### 6.1.5. Efficacy evaluation

The primary analysis will be an intent-to-treat analysis. The standard 95% confidence intervals for treatment differences between each dose and placebo groups will be constructed for the primary efficacy endpoint. Since the study is stratified with respect to the SNAP status, separate confidence intervals will be constructed for each stratum. If there is no interaction between treatment efficacy and SNAP, the two intervals will be combined across the strata to have a global confidence interval for evaluating each dose effect. If the safety profiles for the four dose groups are similar, the recommended dose will be the one with the best efficacy (largest lower bound of the confidence interval).

Similar analyses will be repeated for the secondary efficacy endpoints. For the secondary endpoint analyses, the weekly pain scores will be calculated for each subject. In order to take advantage of such repeated measurements in the analysis, a 95% confidence interval of the difference between a dose group and the placebo will be constructed at each week. These intervals will be combined using the technique by Wei and Johnson25 to obtain a single more informative confidence interval for the treatment difference over the entire study period.

Subjects with greater than 0.35-unit pain improvement on the 13-point Gracely scale at Week 6 will be classified as treatment successes. Treatment group comparisons will be carried out using the Chi-square test and Fisher’s exact test. The standard confidence interval of the difference of the weekly success rates between a dose group and placebo will be constructed. For this dichotomized response, a single interval estimate across the entire study period will be computed using the Wei and Johnson technique.

In addition, an analysis of covariance (ANCOVA) which adjusts for the differences in baseline Gracely pain scale will be conducted for both primary and secondary efficacy endpoints. Primary and secondary efficacy analyses will also be repeated adjusting for other factors that may affect the outcome. Candidate predictive factors are SNAP amplitude at baseline, type of sensory neuropathy (DSP versus ATN), CD4 counts, plasma viral load, age, body mass index (BMI), duration of disease, and background antiretroviral therapy.

Additional efficacy analyses will include per protocol analyses. The previously described statistical approach will be repeated for this population.

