For those subjects in the prosaptide groups who were treatment successes, the mean Gracely pain scale during the crossover placebo period will be calculated. The time at which the mean Gracely pain scale returns to the baseline level will be summarized by treatment group.

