### 6.1.8. Interim analysis

A single interim analysis of the primary efficacy endpoint will be conducted after the first 200 subjects have completed the 6-week double-blind treatment period. Treatment arms determined to have minimal possibility of efficacy in a futility analysis will be dropped from the study. In addition, an estimate of variance of the primary endpoint will be performed and an evaluation of effect of SNAP will be assessed. Because the study will not be terminated due to any premature treatment efficacy, there should NOT be a penalty on the global Type I error rate for this interim look.

For the interim analysis, the standard deviation of the changes of the pain score will be estimated to see if the assumed standard deviation of 0.35 is valid. Next, a “predicted” 95% confidence interval for the treatment difference between each dose and placebo groups will be computed for the primary efficacy endpoint. If the confidence interval for a dose group does not include 0.17 (projected placebo effect, see Section 6.3 for justification), this dose group will be dropped from the study. However, this treatment effect of 0.17 will be re-estimated from the interim analysis data, and the decision rule can be modified based on the new estimate. If subjects with a negative SNAP do not benefit from the treatment, future subjects with a negative SNAP will not be enrolled in the study. Finally, the sample size based on the new estimate of the standard deviation will be determined so that the length of the 0.95 confidence intervals of the difference of changes between a dose group and the placebo will be within 0.24 (twice of 0.12, see Section 6.3 Sample size and power considerations) at the final analysis.

The interim analysis will be performed by CBAR at the Harvard School of Public Health. The results will be shared only with members of the independent Data Safety Monitoring Board (DSMB), who will make recommendations to the Protocol Chair and the study team regarding protocol modifications. In order to avoid bias, the DSMB will not disclose any findings except for issuing a decision statement. All staff, including the Savient clinical team and investigators, involved in the conduct of the study will remain blinded to the results of such analyses.

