## Sample size and power considerations

Based on two studies of neuropathic pain in subjects with HIV-SN20, 21, the average placebo response in the Gracely pain scale is about 0.17, and the standard deviation of the change in Gracely pain scale is approximately 0.35. Therefore, any treatment differences of less than 0.17 can be considered to be not clinically meaningful. This study is designed to detect a minimum treatment difference of 0.17 between any dose group and placebo. In order to have at least 80% power to detect this difference and a significance level of 0.05 (2-sided), 70 evaluable subjects at the end of the trial in the 4 mg, 8 mg, 16 mg and placebo groups are required. The power to detect this difference between the 2 mg and placebo groups will also be calculated before the final efficacy analysis. With 70 subjects per group, the 95% confidence interval for the changes between any dose group and the placebo covers (d-0.12, d+0.12), where d is the observed difference between the two groups. Allowing for early dropouts and assuming the enrollment of 45 subjects in the 2 mg group, 355 subjects will need to be enrolled for the final analysis.

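### Timing loss of effect to the return of mean pain to baseline in treatment successes cannot separate a lasting drug effect from the placebo response that the protocol itself expects

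*Protocol*

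**What the plan says.** Protocol 3.1 states the aim: "The purpose of the crossover period is to assess the duration of prosaptide response after discontinuation of treatment". Section 2.4 lists the matching exploratory measure: "comparison of the duration of treatment effect in the 2-week placebo crossover period (Week 7 through Week 8) among the treatment arms in subjects who" met the success definition. The synopsis repeats it.

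Section 6.1.5 fixes the calculation: "For those subjects in the prosaptide groups who were treatment successes, the mean Gracely pain scale during the crossover placebo period will be calculated", and then "The time at which the mean Gracely pain scale returns to the baseline level will be summarized by treatment group". It defines success thus: "Subjects with greater than 0.35-unit pain improvement on the 13-point Gracely scale at Week 6 will be classified as treatment successes". Section 2.4 has at least 0.35 instead of more than 0.35; the difference does not matter here.

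On what placebo does to pain, section 6.3 says that "the average placebo response in the Gracely pain scale is about 0.17" and that "the standard deviation of the change in Gracely pain scale is approximately 0.35". Section 6.1.8 again uses 0.17 as a placebo effect ("projected placebo effect, see Section 6.3 for justification").

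Under 3.1 and the last paragraph of 6.1, all active arms switch to blinded placebo injections at Visit 7 and the placebo arm switches to 4 mg. That paragraph of 6.1 also plans a summary, for each dose group, of how the Gracely score has changed since Visit 7.

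**The concern.** A measure of how long a drug effect lasts should end at the level expected without the drug. In Weeks 7 and 8 the former active-arm subjects are still receiving blinded injections. On the protocol's own figures, the level without drug is then about 0.17 units better than baseline. Time to baseline therefore mixes loss of drug effect with loss of placebo response.

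Selecting successes adds a second problem. A subject who passes a threshold of 0.35 does so partly through the drug and partly through whatever else lowered that subject's pain at Week 6. To the extent that the second part is stable, it stays when the drug is withdrawn.

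No arm remains on placebo through Weeks 7 and 8, so there is no concurrent picture of the off-drug level. What is at stake is the stated purpose of the crossover: a report could describe a lasting effect that is not due to the drug.

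**Working it through.** **Inputs from the documents.** Mean placebo improvement 0.17, SD of change 0.35, design difference 0.17 (6.3); success threshold 0.35 (2.4, 6.1.5); improvement counted as positive, Week 0 minus Week 6 (6.1).

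**The protocol's own figures first.** It states no figure for time to return to baseline. The inputs 0.17 and 0.35 do reproduce the sample size:
- n per group = 2 × (1.96 + 0.84)² × 0.35² / 0.17² ≈ 67 by the normal approximation, and 68 by the t-test, against 70 stated.
- Power at 70 per group is 0.82, which meets the stated minimum of 80%.
- The 95% half-width is 1.96 × 0.35 × √(2/70) = 0.116, against 0.12 stated.

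**Assumptions not in the documents.** Changes are roughly normal; the drug adds a constant D; the SD is still 0.35 in Weeks 7 and 8; the 0.17 placebo response persists then. The correlation ρ between the Week 6 change and the later change is unknown, so it is varied from 0 to 1.

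**Step 1: who is a success.** Week 6 improvement is N(0.17 + D, 0.35²). With z = (0.35 − 0.17 − D)/0.35, the success rate is P = 1 − Φ(z), and the mean improvement among successes is 0.17 + D + 0.35 × φ(z)/P.
- D = 0: P = 0.304, mean 0.573.
- D = 0.17: P = 0.489, mean 0.626.
- D = 0.34: P = 0.676, mean 0.696.

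Under a constant effect of 0.17, about 0.304/0.489 = 62% of active-arm successes would also have succeeded on placebo.

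**Step 2: remove all drug effect at Visit 7.** The expected later improvement among successes is 0.17 + ρ × (mean among successes − 0.17 − D).

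| Drug effect D | ρ = 0 | ρ = 0.5 | ρ = 0.75 | ρ = 1 |
|---|---|---|---|---|
| 0 (inert) | 0.17 | 0.37 | 0.47 | 0.57 |
| 0.17 | 0.17 | 0.31 | 0.38 | 0.46 |
| 0.34 | 0.17 | 0.26 | 0.31 | 0.36 |

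Every entry is better than baseline. At any positive correlation, the inert dose leaves its successes furthest from baseline.

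**Step 3: sampling variation of the group mean.** With D = 0.17, an arm of 70 has about 70 × 0.489 = 34 successes. At ρ = 0 the chance that a weekly group mean has reached baseline is Φ(−0.17/(0.35/√34.2)), about 0.2%. At ρ = 0.5 or more it is practically nil.

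**Step 4: individual subjects.** With D = 0.17, the share of successes at or past baseline in a given week is Φ(−0.17/0.35) = 31% at ρ = 0. By simulation (2,000,000 subjects per setting) it is 17% at ρ = 0.5 and 8% at ρ = 0.75. At ρ = 1 it is 0%.

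**Step 5: if the placebo response does not persist.** With the 0.17 gone entirely, selection alone still leaves successes 0.5 × 0.286 = 0.14 units better than baseline at ρ = 0.5 for D = 0.17, and 0.5 × 0.403 = 0.20 for an inert dose. The expected mean returns to baseline only if the placebo response vanishes and ρ is also 0.

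**The case against.** The strongest reply is that the measure is exploratory and descriptive. No test or decision depends on it; under 6.1.5 the recommended dose comes from the primary-endpoint intervals and the safety profiles. This stands, and it limits the weight of the point.

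Three stronger readings are tempting, and the documents do not support them.

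- *Nothing in the plan would reveal the problem.* A reader might infer this from the lack of a continued-placebo arm. But 6.1 plans the change since Visit 7 for each dose group, on the Gracely scale, not restricted to successes and not tied to baseline. Sudden loss of a 0.17 effect would appear there as about 0.17 of worsening. An inert dose would be expected to show about none, and no Week 6 advantage over placebo either. That is real mitigation. It leaves the duration measure in 2.4 and 6.1.5 as it is.
- *The mean can never return to baseline within two weeks.* The result depends on the placebo response persisting and on a correlation that the documents do not give (Step 5). Some individual successes would return. Section 6.1.5 does not say whether its mean is per subject or per group, so individual return times could be informative for some subjects.
- *An apparent effect beyond two weeks must be false because the half-life is short.* The dose selection section reports animal data suggesting pain reduction for more than 24 hours despite the short half-life. Half-life therefore does not settle how long the effect lasts.

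Handling of subjects who have not returned by Visit 8 may properly be left to a statistical analysis plan, and is not counted against the protocol.

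**Conclusion.** The point holds in this limited form. On the protocol's own figures, baseline is not the level expected once drug effect has gone, and restricting to successes moves the group further from it. If all drug effect stops at Visit 7 and the 0.17 placebo response persists, the group mean of successes is expected to stay 0.17 to 0.46 units better than baseline for a 0.17 effect, and 0.17 to 0.57 for an inert dose. The ranges span correlations from 0 to 1 and assume normal changes and an additive effect.

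The measure can therefore show an effect lasting beyond two weeks for any dose, including an inert one. It is worth correcting because it is the exploratory measure that serves the crossover's stated purpose. It does not touch the primary analysis or the choice of dose.

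**What to change.** In 2.4 and 6.1.5, and in the matching line of the synopsis:

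- For all active-arm subjects who enter the crossover, estimate the mean change from baseline in Week 7 and in Week 8 by dose.
- Report the difference from the placebo arm's Week 6 change with its 95% confidence interval, alongside the change since Visit 7 already planned in 6.1.
- Do not declare the effect lost merely because the interval includes zero. At the design SD and 70 per group, a fully persistent effect of 0.17 would be called lost about 18% of the time (1 − 0.82). With 40 to 45 subjects in the 2 mg arm against 70 on placebo, this would be about 28 to 31%. Apparent duration would then depend on arm size.
- Keep time to baseline in successes as a descriptive summary, and state that it includes placebo response.

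The cost is analysis wording only, since all the data are already collected. The downside is that the placebo reference comes from Week 6 and is not concurrent with Weeks 7 and 8. The text must say so.

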### 6.1.6. Safety evaluation

The assessment of safety will be based mainly on the frequency of adverse events and on the number of laboratory values that fall outside of pre-determined ranges. The safety measures will also include vital signs, physical examination, neurological examination, HIV-1 RNA, EKG, Karnofsky performance score, nerve conduction studies and prosaptide serum antibodies.

Adverse events will be summarized by presenting, for each treatment group, the number and percentage of subjects having any adverse event, having an adverse event in each body system and having each individual adverse event. Any other information collected (i.e. severity or relatedness to study medication) will be listed as appropriate.

Laboratory data will be summarized by presenting shift tables using extended normal ranges (baseline to most extreme post-baseline value), by presenting summary statistics of raw data and change from baseline values (means, medians, standard deviations, ranges) and by the flagging of notable values (as defined in section 7.1) in data listings. Two (or more)-way frequency tables of changes in laboratory test results in terms of normal ranges at the follow-up visits versus baseline by treatment group, as well as changes in absolute values from baseline will be examined for treatment differences. Change from baseline of plasma HIV-1 RNA levels by treatment group will be specifically evaluated.

Data from other tests (i.e. electrocardiogram or vital signs) will be listed, notable values will be flagged, and any other information collected will be listed as appropriate. Any statistical tests performed, such as the Chi-square test and the t-test, to explore the data will be used only to highlight any interesting comparisons that may warrant further consideration.

### 6.1.7. Statistical methods for pharmacokinetic analysis

The sparse plasma concentration data collected in this study will be utilized in a subsequent population pharmacokinetic analysis using a non-linear mixed effects modeling approach. The software package, NONMEM (NONlinear Mixed Effects Models) version V, Level 1.1 will be used to estimate population means and variances of specific pharmacokinetic parameters, such as clearance (CL) and volume of distribution (V). The relationship between the pharmacokinetics of prosaptide (CL, V) and covariates will be explored. The following covariates will be examined for a possible relationship to prosaptide drug exposure and include but are not limited to: age, body weight, height, body mass index, race, serum creatinine, creatinine clearance (as calculated by Cockcroft-Gault), aspartate transaminase, alanine transferase, alkaline phosphatase, serum albumin, total protein, and concomitant medications.

### 6.1.8. Interim analysis

A single interim analysis of the primary efficacy endpoint will be conducted after the first 200 subjects have completed the 6-week double-blind treatment period. Treatment arms determined to have minimal possibility of efficacy in a futility analysis will be dropped from the study. In addition, an estimate of variance of the primary endpoint will be performed and an evaluation of effect of SNAP will be assessed. Because the study will not be terminated due to any premature treatment efficacy, there should NOT be a penalty on the global Type I error rate for this interim look.

For the interim analysis, the standard deviation of the changes of the pain score will be estimated to see if the assumed standard deviation of 0.35 is valid. Next, a “predicted” 95% confidence interval for the treatment difference between each dose and placebo groups will be computed for the primary efficacy endpoint. If the confidence interval for a dose group does not include 0.17 (projected placebo effect, see Section 6.3 for justification), this dose group will be dropped from the study. However, this treatment effect of 0.17 will be re-estimated from the interim analysis data, and the decision rule can be modified based on the new estimate. If subjects with a negative SNAP do not benefit from the treatment, future subjects with a negative SNAP will not be enrolled in the study. Finally, the sample size based on the new estimate of the standard deviation will be determined so that the length of the 0.95 confidence intervals of the difference of changes between a dose group and the placebo will be within 0.24 (twice of 0.12, see Section 6.3 Sample size and power considerations) at the final analysis.

The interim analysis will be performed by CBAR at the Harvard School of Public Health. The results will be shared only with members of the independent Data Safety Monitoring Board (DSMB), who will make recommendations to the Protocol Chair and the study team regarding protocol modifications. In order to avoid bias, the DSMB will not disclose any findings except for issuing a decision statement. All staff, including the Savient clinical team and investigators, involved in the conduct of the study will remain blinded to the results of such analyses.

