### 3.1.3. Interim analysis

An interim futility analysis will be conducted after the first 200 subjects have completed the 6-week double-blind treatment period. Specifically, an evaluation of the primary endpoint, which is the effect of prosaptide on neuropathic pain compared to placebo during Week 6 of treatment, for each treatment arm will be determined. Treatment arms determined to have minimal possibility of efficacy in the futility analysis will be dropped from the study. In addition, an evaluation of variance of the primary endpoint and effect of SNAP will be assessed. Subjects will be added if required to a maximum of 500 randomized subjects.

Subjects **will continue to be randomized** into the study during the interim data analysis, and follow their assigned treatment regimen to completion. If the interim analysis results in dropping of one or more treatment arms, a protocol amendment will be issued for all subjects randomized subsequently to the interim analysis results. The protocol amendment will detail revised study procedures and drug supply.

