# 6. Statistical methods

## 6.1. Statistical methods

This is a double-blind, randomized, placebo controlled study with five dose groups (0, 2, 4, 8, 16 mg/per day). The primary efficacy endpoint is the change of the Gracely pain average score during Week 6 from the Week 0 baseline level (Week 0 minus Week 6 score). The primary objective is to select at least one dose group which is significantly better than the placebo with respect to this endpoint. Furthermore, the dose response relationship among these four groups will be examined.

Due to the slow enrollment, the protocol is amended to restrict further enrollment in the lowest dose arm (2 mg). It is expected that a sufficient number of subjects will have been treated at 2 mg before the amendment is fully implemented. An inferential statistical comparison between the 2 mg and placebo groups will still be carried out if there is a sufficient statistical power to detect a clinically meaningful treatment difference. Regardless, all dose groups will be used to characterize safety and dose response.

The study will be stratified with respect to SNAP (+ or -). For each stratum, a random treatment allocation rule will be utilized so that the balance among these five dose groups (four dose groups after the amendment) within each center will be maintained during the study.

It is planned that the data from all centers that participate in this protocol will be combined, so that an adequate number of subjects will be available for analysis. The results from each center will also be presented individually. In addition, it is planned that the data from both SNAP positive and SNAP negative subjects will be combined in the final analysis if there is no interaction between treatment effects and SNAP status.

The significance for all statistical tests will be reported at the p=0.05 level, and all tests will be 2-sided. Each dose group will be compared to the placebo group and a 95% confidence interval for each comparison will be provided. Because this is a phase 2 study, no adjustments for multiplicity will be made.

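### The interim futility rule gives no direction, so a dose whose interval lies wholly above 0.17 also meets the written condition for being dropped

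*Protocol*

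**What the plan says.** Section 6.1.8 (Interim analysis) sets a single look after 200 subjects have completed the 6-week double-blind period. A predicted 95% "confidence interval for the treatment difference between each dose and placebo groups will be computed for the primary efficacy endpoint". The decision rule comes next, as a condition: "the confidence interval for a dose group does not include 0.17 (projected placebo effect, see Section 6.3 for justification), this dose group will be dropped". The sentence after it adds that "this treatment effect of 0.17 will be re-estimated from the interim analysis data, and the decision rule can be modified based on the new estimate".

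The purpose is stated as futility. Section 3.1.3 says: "Treatment arms determined to have minimal possibility of efficacy in the futility analysis will be dropped from the study". Section 6.1.8 repeats this, and the synopsis has the same intent. Section 6.1.8 also waives any Type I error penalty on this ground: "Because the study will not be terminated due to any premature treatment efficacy".

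Two other places fix the meaning of the numbers. Section 6.1 defines the primary endpoint as "Week 0 minus Week 6 score". Section 6.3 designs the study to detect a difference of 0.17, calls anything smaller not clinically meaningful, and assumes an SD of 0.35 with 70 evaluable subjects per group.

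**The concern.** A positive Week 0 minus Week 6 change is an improvement, so a positive dose-minus-placebo difference favours the dose. An interval can fail to contain 0.17 in two ways. If it lies wholly below 0.17, the dose is unlikely to reach the meaningful difference, and that is futility. If it lies wholly above 0.17, the dose appears to exceed the target. The written condition treats both alike. No section supplies a one-sided version: the synopsis and Sections 3.1.3 and 4.1 give the futility purpose without a numerical criterion.

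At stake is enrolment to an effective dose. Section 3.1.3 provides that subjects randomized after the interim result would come under an amendment without the dropped arm. That dose would finish with fewer subjects and a wider interval. Section 6.1.5 recommends, given similar safety, the dose whose interval has the highest lower limit, so a wider interval counts against it.

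**Working it through.** **Inputs from the protocol.** Difference 0.17, SD 0.35, 70 evaluable per group, two-sided 0.05, power at least 80%, interval half-width 0.12 (Section 6.3); interim at 200 completers (Section 6.1.8); five groups (Section 6.1).

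**Assumptions.** 40 per arm at the interim (200/5), with 36 to 50 as a range because the 2 mg arm is being curtailed. The protocol does not define the predicted interval, so three readings are shown.

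**The plan's own figures reproduce.** Half-width at 70 per group: 1.96 × 0.35 × √(2/70) = 0.116, which rounds to 0.12. Power at 70 per group for 0.17 is 82% (normal approximation) or 81% (t-test). The sample size is not in question.

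**Rule as written.** The SE of the interim difference d is 0.35 × √(2/40) = 0.0783. With half-width h, a dose is dropped if d < 0.17 − h or d > 0.17 + h. The chance of being dropped from above is 1 − Φ((0.17 + h − true difference)/SE).

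- Reading A, the interim interval itself: h = 1.96 × 0.0783 = 0.153. Drop if d < 0.017 or d > 0.323.
- Reading B, the interim estimate with the half-width expected at 70 per group: h = 0.116. Drop if d < 0.054 or d > 0.286.
- Reading C, a final estimate projected with the remaining 30 per arm at the design effect of 0.17: the final-n half-width is scaled by 70/40, so the upper drop point is 0.17 + 0.116 × 70/40 = 0.373.

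| True difference | A: dropped from above | B: dropped from above | C: dropped from above |
|---|---|---|---|
| 0.17 | 2.5% | 6.9% | about 0.5% |
| 0.25 | 17% | 32% | about 6% |
| 0.35 | 63% | 79% | about 38% |

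**Symmetry.** The condition depends only on the distance of d from 0.17. True differences of 0 and 0.34 are equally far from 0.17, so a dose with no effect and a dose with twice the design effect are equally likely to be dropped: 58% each under A and 76% each under B. Over 36 to 50 per arm these become 54–68% and 74–78%.

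**Upper-limit rule.** Dropping only when the upper limit is below 0.17 keeps the lower cut-offs (d < 0.017 under A, d < 0.054 under B). The chance of dropping a dose with no effect stays at 58% or 76%. At a true difference of 0.17 it is 2.5% or 6.9%, and at 0.34 it is below 0.1%.

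**Cost to a wrongly stopped dose.** Suppose it ended with 40 subjects against 70 on placebo. The SE would be 0.35 × √(1/40 + 1/70) = 0.069 and the half-width 1.96 × 0.069 = 0.136, against 0.116 with 70 in each group. Its lower limit would be about 0.02 lower for the same estimate. Subjects already randomized finish treatment, so the arm would probably hold more than 40 and lose somewhat less.

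**The case against.** The strongest reply is that the intent is plain. The same section speaks of futility and rules out stopping for efficacy, and Section 6.3 makes 0.17 a floor of relevance, so only an interval below 0.17 makes sense as a reason to drop a dose. The rule does not execute itself either: CBAR runs the analysis, the DSMB makes recommendations, and dropping an arm needs an amendment. This makes literal application less likely, and it stands to that extent. It does not correct the sentence, which is the only numerical criterion in the protocol. The sponsor's team and the investigators stay blinded and receive only a decision statement, so they could not see on which side an arm had failed. The clause allowing the rule to change concerns re-estimation of 0.17 and adds no direction.

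The size is also fairly challenged. The large percentages need true differences well above the design value, and they depend on an interval that the protocol does not define.

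A reader might infer that the final analysis would be left to choose among weaker doses and so give the wrong dose-ranging answer. The documents do not support that. Section 3.1.3 lets randomized subjects complete their assigned regimen, Section 6.1.1 keeps treated subjects with follow-up in the intent-to-treat population, and nothing says that a dropped arm leaves the final comparison. The curtailed 2 mg arm stays in the dose-response description and is tested if power allows. A reader might also extend the defect to the sentence on closing enrolment of SNAP-negative subjects. That sentence turns on absence of benefit, so it already has a direction.

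**Conclusion.** The rule is wrong as written and should be corrected before the interim look. It contradicts the futility purpose stated in the synopsis, in Section 3.1.3 and in Section 6.1.8 itself. With 40 per arm and an SD of 0.35, the upper-side risk is small at a true difference of 0.17 (about 0.5–7% across the three readings). It rises as the dose improves, to about 6–32% at 0.25 and 38–79% at 0.35. These figures are conditional on the assumed effect, the interim numbers and the reading of the predicted interval. That the rule acts on both sides of 0.17 does not depend on any of them.

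The supported consequence is stopped enrolment to an effective dose, lost precision for it, and a handicap in dose selection. The documents show neither an intention to discard superior doses nor exclusion of a dropped arm from the final analysis.

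**What to change.** Replace the decision sentence in Section 6.1.8 with:

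> If the upper limit of the predicted 95% confidence interval for dose minus placebo lies below 0.17 (or the re-estimated value replacing it), this dose group will be dropped from the study.

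The bracketed words keep the sentence consistent with the re-estimation clause that follows it. The SNAP-negative sentence needs no change for this purpose. Any DSMB or CBAR working document that repeats the rule should be brought into line; none is available here, so whether one does is unknown.

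The cost is one sentence, agreed before the interim data are seen. It needs no additional patients or data and does not lower the chance of dropping a dose with no effect.
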